The Ghana Heart Initiative (GHI) initiated in September 2018, and offi cially launched on 9th January 2019, introduced an innovative health system intervention to strengthen early detection, and management of hypertension and CVD across health facilities in the Greater Accra Region (GAR). The initiative was implemented as a collaborative effort by the Deutsche Gesellschaft für Internationale Zusammenarbeit (GIZ) GmbH, Ministry of Health (MoH) and the Ghana Health Services (GHS). The GHI (“the intervention”) enables frontline healthcare workers to better address the needs of patients and communities and support advocacy and policy that promotes effective care for CVD. The intervention does not target the single patient but changes the quality of care given to the single patient, by changing the way the health system addresses the management of risk factors (such as hypertension) and CVD. The overarching goal of this study is to conduct a rigorous evaluation of the GHI, a supply-side intervention implemented in 42 diverse health facilities (primary to tertiary care level) for the prevention and management of hypertension and CVD in the GAR, adopting a mixed-methods implementation science approach.

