### Study intervention

The first phase of the GHI, a three-year (2018–2020) programme funded by Bayer AG and implemented through the GIZ, was designed to improve risk assessment and management of hypertension and CVD in public health facilities and hospitals in the GAR. Its primary objective was to improve prevention, detection or diagnosis, and management of CVD. The GHI includes five main components: (i) Stakeholder engagement and development of national guidelines for the management of CVD, (available in hard copies and a digital app); (ii) Training of healthcare workers coupled with coaching / mentorship visits; (iii) Equipment supplies for the diagnosis and treatment of CVD; (iv) Training of healthcare workers for the collection of facility-level data for programme monitoring and the GHI programme team worked with the Policy, Planning, Monitoring and Evaluation Division of the GHS to include important NCD indicators including CVD in the District Health Information Management System (DHIMS2) to facilitate facility-level routine data collection and reporting; and (v) Establishment of a round the clock (“24/7”) CVD support center.

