For the provider KAP survey and exit survey, the field data collection team(s) visit a health facility and capture a random sample of healthcare providers and patients available on the day of the visit. This method relies on random sampling and the effi ciency of the field team. In essence this means maximizing the number of potential respondents to be interviewed on the day of the visit i.e. all eligible patients exiting the facility are interviewed, all eligible healthcare providers present and available at the facility are interviewed [28] [29]. The field work is carefully timed so that it coincides with the day of a hypertension / CVD clinic. Prespecified **eligibility criteria** is applied for health facilities and study participants (providers and patients) for the quantitative evaluation. The health facility assessment survey is carried out in all GHI intervention facilities, and matched control health facilities to specific characteristics (example, level of care, volume of patients attending the clinic, bed size, human resources available, etc.). The provider survey is recruiting providers (doctors, nurses, physician assistants, pharmacists) aged 18 years and above, both males and females; presently working in the facility at least from the last 3 months. Further, a licensed provider is defined as a physician or a nurse, pharmacist or physician assistant who is directly involved in providing CVD related services (counseling, health education, or consultation services or pharmacological therapy). The provider survey excludes those healthcare workers who have a managerial position and do not provide any patient care. Also, a physician, nurse or pharmacist who has worked in the facility for less than 3 months is excluded from the provider survey. The patient exit survey is carried out among those aged 18 years, both males and females, and having physician diagnosis of hypertension or other CVD conditions. The exclusion criteria include patients having diseases associated with frequent hospitalization (advanced cancer, end stage renal disease) bedridden or debilitating conditions. The MRR is performed for the patient folders for those aged 18 years and above, both males and females, and having physician diagnosis of hypertension or CVD conditions-Medical records from 2018 to 2022 are being reviewed. The medical records of pregnant women and those patients having diseases associated with frequent hospitalization (advanced cancer, end stage renal disease); bedridden or debilitating conditions are excluded for the MRR.

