The medical records of outpatient and inpatient folders at two cross-sectional timepoints before and after GHI implementation are being reviewed to assess between group differences in hypertension and CVD care delivery. Eligibility of medical records are pre-specified based on confirmed diagnosis of hypertension or CVD, and complete medical records with at least data available on patient demographics (age, sex), medical history (confirmed case of hypertension or CVD), laboratory results (any test prescribed, or test reports reviewed), and medical treatment or prescription.

Lastly, DHIMS2 data routinely collected by the MoH in Ghana to monitor service provision consisting of monthly facility-specific counts for a wide range of services, including CVD will be analyzed to assess the differences in care delivery between the intervention and control health facilities over the time period. In line with prior work, to translate monthly counts into indicators that adequately capture service coverage, we construct outcome variables that account for the underlying target population living in the catchment area of a given facility [32]. More specifically, we apply interrupted time series analysis to DHIMS2 data to assess impact on the following CVD indicators: prevalence of hypertension, coronary heart disease, stroke, heart failure and related mortality.

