Next, when analyzing the KAP survey we will report the demographic characteristics of healthcare providers by the intervention and control arm facilities, reporting the mean (standard deviations, SD) or median (25th and 75th percentiles) for continuous variables and frequencies (percentages) for categorical variables. Knowledge about CVD symptoms and modifiable risk factors will be reported as number (percent) by overall and intervention and control arm facilities. Next, each correct response for knowledge related questions will be assigned a score of 1 and the total score for the knowledge of CVD risk factors and treatment recommendations will divided by tertiles and classified as minimal, moderate, and high knowledge. The mean (SD) for knowledge of CVD risk factors and treatment will also be reported by intervention and control facilities. Finally, the correct scores for the knowledge of CVD risk factors and treatment strategies will be classified into high knowledge (> 75% correct responses) and poor knowledge (≤ 75% correct responses) using arbitrary threshold for comparison and also informed by the published literature [35] [36]. The chi-square test will be performed to investigate the difference in knowledge scores between intervention and control arm facilities across age-group, sex, and education strata. Bivariable and multivariable regression analyses will be performed to assess the factors associated with high knowledge of CVD symptoms, and modifiable risk factors. The unadjusted and adjusted odds ratio with 95% confidence intervals (CI) will be reported. The model will be adjusted for age, sex, type of health facility and type of healthcare worker.

Lastly, an interrupted time-series analyses (ITSA) is carried out to establish effects of the GHI on the screening, diagnosis, and management of hypertension / CVD, if aggregate facility-level monthly data are available from the DHIMS2. ITSAs apply segmented regression to assess the impact of events that have occurred at a clearly defined point in time. Data points recorded in the GHI enabled DHIMS2 system will be analyzed by month to examine trends over time and seasonality. We will also evaluate change in patient outcomes over time (e.g., mean systolic BP change).

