### Evaluation Design Strengths and Weaknesses

The mixed-methods triangulation study is the first of its kind for LMICs and in sub-Saharan Africa, testing a comprehensive and multifaceted health system intervention addressing hypertension and CVD management. The evaluation is rigorously designed, factoring in multiple data sources, minimizing biases using matched control health facilities, data triangulation using quantitative survey and qualitative interview data, and economic evaluation. The ToC was developed in a participatory manner in collaboration with GHI programme implementers helping the evaluators to understand where the intervention tried to produce a change and led to a commonly defined TOC and definition of indicators. Our focus is centered more on a theory-driven evaluation and the fact that we will work “closer to reality” but far from a real experiment or quasi-experiment. To avoid contamination between the intervention and control facilities, the data collection for control group facilities and participants will be accomplished by a separate team of trained field enumerators. However, in a real-world setting we cannot avoid spillover of intervention components to other regions since the national guidelines for the management of CVD were signed by the Minister of Health in 2021 and offi cially launched in August 2022 by the MoH and is available in the public domain and can be accessed via the AkomaCare App (https://akomacare.org/download) [47]. The data collection timepoints for the MRR before and after GHI implementation has been prespecified in both the intervention and control health facilities to avoid any seasonal variations in the hypertension and CVD care outcomes. Furthermore, we customized the survey questionnaires developed with an open-source platform called Survey Solutions (https://mysurvey.solutions/en/) developed by the World Bank. Data is entered on Android-based tablets using the Survey Solutions Interviewer App, stored locally on the tablets, and synchronized regularly to HIGH’s virtual server, enabling real time tracking and remote data monitoring. The Survey Solutions Designer allows the inclusion of instructions visible in blue for each question as the interviewer progresses through the survey. This digital data collection approach along with its technical features improves data quality and reduces data entry errors or missing values.

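### The DHIMS2 interrupted time series measures GHI with a recording system that GHI itself changed, and no single interruption date is fixed

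*Protocol article*

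**What the plan says.** The Statistical analysis section describes the ITSA this way: "ITSAs apply segmented regression to assess the impact of events that have occurred at a clearly defined point in time". It names the data source: "Data points recorded in the GHI enabled DHIMS2 system will be analyzed by month to examine trends over time and seasonality". The analysis is conditional on aggregate monthly facility data being available. Under Data collection Tools, Indicators, and Strategies, the ITSA is to "assess impact on the following CVD indicators: prevalence of hypertension, coronary heart disease, stroke, heart failure and related mortality". Monthly counts are scaled to the catchment population, and DHIMS2 data are to be compared between intervention and control facilities over time. The Conceptual framework section expects the ITSA, where data permit, to support attributing causality to GHI.

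Study intervention lists as GHI's fourth component the training of health workers to collect facility-level data, together with work with a Ghana Health Service division "to include important NCD indicators including CVD in the District Health Information Management System (DHIMS2) to facilitate facility-level routine data collection and reporting".

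On timing, Background says GHI was "initiated in September 2018" and officially launched on 9 January 2019. Study intervention calls the first phase a three-year programme, 2018–2020. Evaluation Design Strengths and Weaknesses says the national guidelines were signed in 2021 and launched in August 2022, and concedes that "we cannot avoid spillover of intervention components to other regions since the national guidelines for the management of CVD were signed".

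**The concern.** A time series can show an effect only if the outcome is recorded the same way before and after the interruption. Here recording is part of what was delivered. If trained facilities record more of the hypertension and CVD cases they already see, monthly counts rise with no change in care. Dividing by catchment population does not help, because the denominator carries no information on completeness. Neither the Statistical analysis section nor the discussion of weaknesses and limitations names this threat.

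The second problem is the boundary. The article states that the method needs a clearly defined moment, names none for the analysis, and reports several dates. With an effect that builds up, the estimated level and slope depend on which date is used.

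Third, the outcome list under Data collection frames recorded prevalence as impact, whereas Study outcomes makes newly diagnosed patients a primary outcome. A rise can be the intended gain in detection. It cannot be read as a change in disease burden.

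At stake is whether the ITSA can carry the causal reading given to it in the Conceptual framework section.

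**Working it through.** The article gives no ITSA figure (no interruption date, series length, effect size or power), so there is nothing to reproduce. The calculations below only illustrate the possible size of the problem.

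**Inputs from the article.** Initiation September 2018; launch 9 January 2019; first phase to the end of 2020; guideline launch August 2022. September 2018 to January 2019 is 4 months, and September 2018 to August 2022 is 47 months.

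**Assumptions, not from the article.** Recording completeness is 60% before GHI and 70%, 80% or 90% after, with no clinical change. The series has 72 months, January 2017 to December 2022, without noise. The model is segmented regression on the log count with a level and a slope change.

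**1. Raw counts.** False ratio = completeness after / completeness before.
- 0.70/0.60 = 1.17
- 0.80/0.60 = 1.33
- 0.90/0.60 = 1.50

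**2. Fitted level change, intervention series alone.** Completeness rises linearly over the 4 months from September 2018.
- Break at September 2018: 1.14, 1.27, 1.40
- Break at January 2019: 1.12, 1.24, 1.35

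**3. Controlled series, controls gaining half as much.** Controls end at 65%, 70% and 75%. The long-run ratio of the arms is 0.70/0.65 = 1.08, 0.80/0.70 = 1.14 and 0.90/0.75 = 1.20. The fitted level change, with the same 4-month rise and the break at September 2018, is 1.06, 1.12 and 1.16. If controls gained exactly as much, the ratio would be 1.00 and the artefact would vanish.

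**4. Slower recording gain.** If the rise takes 28 months instead of 4, the controlled level change at September 2018 falls to 1.02, 1.03 and 1.05. Part of the artefact then appears as a yearly slope change of 1.02, 1.03 and 1.04. The bias moves between terms and does not disappear.

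**5. Choice of date.** Suppose a true ratio of 1.20 builds up linearly on the log scale over the 28 months from September 2018, with perfect recording.

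| Break placed at | Level change | Slope change per year |
|---|---|---|
| September 2018 | 1.04 | 1.05 |
| January 2019 | 1.06 | 1.04 |
| January 2021 | 1.04 | 0.95 |
| August 2022 | 0.96 | 0.96 |

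Between September 2018 and January 2019 the answers are close. The slope change reverses direction once the break is placed at or after the end of the programme. The gradual build-up is itself an assumption, since the article gives no facility schedule.

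**The case against.** The strongest reply is that a control series is already indicated under Data collection Tools, Indicators, and Strategies. The DHIMS2 indicators were added with a national body, so a form change reaching all regions would largely cancel. That is right for a shared change. It does not cover training in data collection delivered under GHI, and the article does not say whether control facilities received the new indicators.

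A second reply is that 9 January 2019 is a usable date, and that lags and transition windows belong in an analysis plan that is not shown. This has some force. What remains is that the article states a requirement and then gives dates that do not meet it without a choice. The ITSA is also conditional and one part of a triangulated evaluation, and the discussion itself calls the work far from a quasi-experiment. That limits the weight of the point but sits badly with the causal wording.

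Several stronger readings are tempting, and the documents do not support them.
- A reader might infer that the analysed indicators have no pre-period. The article does not say which indicators were added, or when.
- A reader might take "Medical records from 2018 to 2022 are being reviewed" to mean that the record review mixes exposed months into its baseline. The article describes two cross-sectional time points, before and after GHI, prespecified in both arms to avoid seasonal variation. The year range is only the outer limit.
- A reader might call guideline spillover concealed. It is disclosed, though not carried into the ITSA. Only the guidelines are said to have become public, and the article does not date when public access began.
- A reader might describe GHI as phased in across facilities. That is an inference from the dates.

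**Conclusion.** The point holds for the DHIMS2 ITSA. The intervention changed the instrument, the control comparison removes only changes common to both arms, and the article neither names this threat nor fixes an interruption date. Followed as written, the analysis could report a recording gain as an effect of GHI.

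The size cannot be derived from the documents. Under the stated assumptions (60% rising to 70–90%), the false ratio is 1.17–1.50 in raw counts. In a controlled series where controls gain half as much over a 4-month rise, it is about 1.06–1.16. It is smaller in the level term if the gain is slower, and nil if both arms gain equally. The point does not extend to the medical record review or the surveys.

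**What to change.** In the Statistical analysis section:

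- Limit the causal ITSA to DHIMS2 indicators reported with an unchanged definition in both arms before September 2018.
- State that it is the controlled comparison already implied under Data collection Tools, Indicators, and Strategies.
- Add sensitivity analyses using monthly reporting completeness and a non-CVD negative-control series.
- Fix one interruption date, with a transition window covering at least September 2018 to January 2019. Fit a ramp over the programme period as a sensitivity analysis.
- Repeat the analysis without the months from August 2022 onward.
- Report a rise in recorded prevalence as detection, not as a change in disease burden.

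If no indicator qualifies, withdraw the causal claim for the ITSA in the Conceptual framework section and present the series descriptively.

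The cost is revised wording, date filters and extra runs on routine data. Completeness and negative-control series would have to be requested with the same extract. The downside is fewer eligible indicators and some lost months. Dropping the whole period from September 2018 to December 2020 is not recommended as the main analysis, because it discards the programme phase itself.

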### Qualitative study component

We propose to conduct qualitative in-depth interviews with policymakers, health administrators, providers, and patients to understand the fidelity, barriers, and facilitators of implementing the GHI in the local healthcare context. For assessing implementation fidelity, semi-structured key informant interviews with policymakers, health administrators and GHI training of trainers are being carried out. Additionally, overall direct and indirect experience with the intervention is explored through in-depth interviews with healthcare providers and patients. Participants are selected purposively, allowing for the researcher to select key informants who will have experience of CVD policy and useful perspectives on the GHI. To enhance the credibility of this sampling, a maximum variation sample is used to ensure the consideration of key demographic variables likely to have an impact on participant’s views, for example, age, and occupation. This aims to ensure that the sample within the selected groups is both diverse and representative of the stakeholders in question, and so maximize a fair share of perspectives and views. Additional participants may be selected using purposive snowball sampling [37]. Data saturation is considered to determine the number of interviews. For conducting the interviews, semi-structured interview guides have been developed for each participant group, and clustered into broad themes to encourage participants to speak freely about their perceptions, experiences and visions. Follow-up questions are prompts and probes aimed at following respondents’ answers and investigating the raised issues more in-depth. In general, the same areas will be covered with every participant so there is some point of comparison, however the topic guide will be adapted for each participant group (in each region). Some participants might be interviewed multiple times. All individual interviews are being audio-recorded and transcribed verbatim by local field researchers and social scientists.

### Qualitative data analysis

Transcripts from individual interviews and key-informant interviews will be analyzed using thematic analysis [38] and will focus on explaining observed heterogeneity and identifying enablers and barriers of the intervention and hypertension and CVD management, with a specific focus on fidelity, implementation and sustainability. We rely on a mixed deductive and inductive approach [39]. An initial set of coding categories are developed based on the themes of the interview guides but will allow additional codes and themes to emerge as we proceed with reading and analyzing the transcribed material. Analyzing data jointly across sources implies that source triangulation is applied [40]. In addition, analyst triangulation [41] is applied since we will ensure that at least two distinct people code and analyze the transcribed material and any discrepancies will be resolved by direct consultation with a third coder. A senior researcher not involved in data collection will review the coding consistency. An expert has given a workshop on the NVivo software to the research staff in order to establish a common platform for the data analyses throughout the study. Data analysis is conducted by the lead qualitative researchers with support from NVivo software version 12.0 (QSR International Pty Ltd, Melbourne, Australia, 2010) [42]. Strategies to collect trustworthy data is guaranteed in the following ways: (1) review the interview guide and coding scheme by HIGH / UGMS core research team; (2) accompany the field researchers during the initial interviews by experienced qualitative researchers (3) review of selected transcripts by senior scientists for triangulation; (4) discussions with and feedback from trained data collectors and evaluation team on emerging themes. Finally, reflexivity includes examining researchers’ own conceptual lens, explicit and implicit assumptions, preconceptions and values and how these affect research decisions in all phases of the qualitative study.

Finally, outcome data is contrasted with implementation data and quantitative and qualitative results obtained from different information sources to validate and complement our findings is triangulated

